#### Neuroimaging data analysis

2.9.2

Neuroimaging data will be analyzed according to standardized pipelines, with comprehensive details provided in Supplementary material 3. For VBM, the CAT12 toolbox (SPM12, version r1720; CAT12, r1720) will be used for bias correction, tissue segmentation, and spatial normalization to MNI space. Whole-brain VBM results will be reported at cluster-level family-wise error (FWE) corrected *p* < 0.05 with an initial voxel-level threshold of *p* < 0.001. Resting-state fMRI data will be preprocessed using DPABI v6.1. Preprocessing will include discarding the first 10 volumes, slice timing correction, realignment, normalization to MNI space, spatial smoothing (6-mm FWHM), nuisance regression (Friston-24 motion parameters and WM/CSF signals), detrending, and bandpass filtering (0.01–0.08 Hz). Volumes with framewise displacement (FD) > 0.5 mm will be censored using scrubbing regressors; participants with >20% censored volumes or with maximum head motion >3.0 mm translation or 3.0° rotation will be excluded. Seed-based functional connectivity will be computed using predefined seeds from the Automated Anatomical Labeling (AAL) atlas (bilateral putamen, caudate, globus pallidus, and thalamus; seed coordinates are provided in Supplementary material 3). Voxel-wise connectivity maps (Fisher's z-transformed) will be assessed using cluster-level FWE correction (voxel *p* < 0.001; cluster *p* < 0.05). To address multiple comparisons arising from testing multiple seeds, seed-level multiplicity will be controlled using false discovery rate (FDR; Benjamini–Hochberg) across seeds (*q* < 0.05). In addition, the bilateral putamen will be designated *a priori* as the primary seed of interest, whereas results from the remaining seeds will be considered secondary/exploratory and interpreted with FDR control across seeds. DTI data will be processed using DTIStudio v3.0.3 (and the NODDI toolbox in MATLAB R2013b, if applicable). Fractional anisotropy (FA), mean diffusivity (MD), radial diffusivity (RD), and axial diffusivity (AD) will be computed. Regions of interest (substantia nigra, putamen, caudate) will be manually delineated on FA color maps by two independent raters blinded to group and time point, with inter-rater reliability assessed using intraclass correlation coefficients (ICC; ICC > 0.80 required). ROI-based statistical comparisons will apply Bonferroni correction within each predefined ROI family. SWI phase images will undergo high-pass filtering (32 × 32) before manual delineation of substantia nigra (SN) area and measurement of SN pars compacta (SNc) width. NM-MRI SNc width will be measured in the dorsoventral direction on the optimal axial slice using the ADW4.6 workstation. ICC will be assessed for all manual measurements, and the average of the two raters will be used for analysis. All statistical tests will be two-tailed with significance set at *p* < 0.05 after correction.

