#### Clinical outcomes

2.6.1

This trial is primarily designed to detect neuroplastic changes via multimodal MRI. Accordingly, the primary endpoint is the change in multimodal MRI biomarkers, whereas all clinical outcomes and biomechanical indices are designated as exploratory endpoints.

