##### Diffusion tensor imaging (DTI)

2.6.2.3

DTI quantifies microstructural integrity and evaluates the microstructural integrity of nigrostriatal pathways through water diffusion anisotropy (34). Reduced fractional anisotropy (FA) in the substantia nigra, putamen, and caudate reflects dopaminergic degeneration, serving as an early biomarker for connectivity disruption and disease progression (35). Imaging Protocol: SMS-DTI sequence: TR/TE = 4,200/72 ms, ST/SG = 2/1 mm, voxel size = 2 mm3, 99 diffusion directions, b-values = 0–3,000 s/mm^2^ (gradient distributions: 0, 300, 350, 650, 950, 1,000, 1,350, 1,650, 1,700, 2,000, 2,700, 3,000).

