#### Clinical data analysis

2.9.1

All statistical tests will be two-tailed, with significance set at α = 0.05. Baseline demographic and clinical characteristics will be summarized descriptively by group. Baseline demographic and clinical characteristics will be summarized descriptively by group. To assess baseline comparability among the three randomized groups, one-way ANOVA (or Kruskal–Wallis test) will be used for continuous variables, and chi-square tests for categorical variables. If significant between-group differences are observed at baseline, the affected variables will be included as covariates in subsequent analyses to adjust for potential confounding. For the primary clinical outcome, no correction for multiple comparisons is applied as this is a single predefined comparison. For secondary clinical outcomes, we will apply False Discovery Rate (FDR) correction within each assessment scale. Continuous data will be analyzed via one-way ANOVA (normally distributed data) or the Kruskal–Wallis *H*-test (non-normal data), with Bonferroni-adjusted *post-hoc* comparisons. Categorical variables will be analyzed using the Pearson χ^2^ test or Fisher's exact test for unordered variables, and the linear trend χ^2^ test for ordered variables. Analysis of covariance (ANCOVA) will be employed to adjust for baseline values, age, disease duration, and levodopa equivalent daily dose where appropriate. If significant baseline differences between groups are observed after randomization, these variables will be included as covariates in the corresponding models to mitigate bias. Missing data will be handled using multiple imputation by chained equations under the missing at random assumption, with sensitivity analyses comparing imputed results to complete-case analyses. An intention-to-treat (ITT) analysis will include all randomized participants, whereas per-protocol analyses will exclude non-compliant cases (< 80% session attendance).

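### The ROI comparisons, DTI among them, use plain Bonferroni; Holm gives the same family-wise error control and is never less powerful

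*Protocol article*

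**What the plan says.** Section 2.6.1 of the protocol article states that "the primary endpoint is the change in multimodal MRI biomarkers", and DTI is one of the modalities listed in section 2.6.2. Section 2.9.2 then fixes three things for DTI:

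- Metrics: "Fractional anisotropy (FA), mean diffusivity (MD), radial diffusivity (RD), and axial diffusivity (AD) will be computed". None is named as primary.
- Regions: "Regions of interest (substantia nigra, putamen, caudate) will be manually delineated on FA color maps by two independent raters".
- Multiplicity: "ROI-based statistical comparisons will apply Bonferroni correction within each predefined ROI family".

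Imaging tests are two-sided at 0.05 after correction. For further detail the section refers to a supplement ("with comprehensive details provided in Supplementary material 3"), which is not at hand.

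Two other places bear on the point. Section 2.6.2.3 gives a rationale for one DTI metric only: "Reduced fractional anisotropy (FA) in the substantia nigra, putamen, and caudate reflects dopaminergic degeneration". For resting-state fMRI, section 2.9.2 does rank its tests: it names the bilateral putamen "as the primary seed of interest, whereas results from the remaining seeds will be considered secondary/exploratory". No such ranking is given for the DTI metrics.

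**The concern.** Section 2.3 plans for at least 20 patients per group after attrition. At that size the threshold for each regional test largely decides what can be detected, and single-step Bonferroni is stricter than it needs to be. It holds every test in the family to 0.05 divided by the family size, even after other tests in the family have been rejected. A uniformly better procedure with the same guarantee has been standard for decades and needs no further assumption about how the tests are correlated.

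A second, smaller matter is that four metrics are computed with no stated order of importance. One of them is redundant: for the diffusion tensor, MD = (AD + 2 x RD)/3 exactly. Only FA is given a reason for being studied. At stake is some avoidable loss of power in one part of the primary endpoint.

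**Working it through.** **Inputs from the article.** Two-sided alpha 0.05; three regions; four metrics; 20 evaluable per group, 10% attrition, three groups. The stated sample size reproduces: 20/0.9 = 22.2, rounded up to 23; 23 x 3 = 69. No DTI effect size, standard deviation, correlation or power is given, so there is no DTI power figure to reproduce. All effect sizes and correlations below are assumptions.

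**Step 1: the two rules.** Order the m p-values in a family as p(1) <= ... <= p(m).
- Bonferroni rejects every p <= 0.05/m.
- Holm compares p(1) with 0.05/m, p(2) with 0.05/(m-1), ..., p(m) with 0.05, and stops at the first failure.

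For m = 3 the Holm thresholds are 0.05/3 = 0.0167, 0.05/2 = 0.025 and 0.05; Bonferroni uses 0.0167 three times. Every Holm threshold is at least 0.05/m, so anything Bonferroni rejects Holm also rejects.

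**Step 2: error control is the same.** Let m0 of the m hypotheses be true nulls. When Holm first rejects a true null, at most m - m0 hypotheses have been rejected before it, so the threshold in use is at most 0.05/m0. The chance that any of the m0 null p-values falls at or below 0.05/m0 is at most m0 x 0.05/m0 = 0.05, whatever their correlation.

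**Step 3: size of the gain.** Simulated two-sample t tests, verum versus sham, n = 20 per arm, the same effect d in every test, correlation 0, 0.3 and 0.6 between tests:

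| Family | d | Bonferroni, power per test | Holm, power per test |
|---|---|---|---|
| 3 regions | 0.6 | 29% | 33-34% |
| 3 regions | 0.9 | 64% | 71-73% |
| 12 tests | 0.6 | 14% | 16-18% |
| 12 tests | 0.9 | 43% | 53-55% |

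The exact noncentral-t values agree with the Bonferroni column: 28.5% and 63.5% at 0.05/3, 14.3% and 43.2% at 0.05/12. For three regions the gain is about 4 to 5 points at d = 0.6 and 8 to 10 points at d = 0.9. If only one of the three regions responds, power in that region changes by less than one point, because the later, looser thresholds are seldom reached.

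**Step 4: what redundancy contributes.** For one region and an effect with 80% power at 0.05 (d = 0.909, n = 20), power is 60% at 0.05/4 and 65% at 0.05/3 (60.2% and 64.5% before rounding). Dropping MD alone from a four-metric family therefore recovers about 4 points.

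**Step 5: how far the family definition matters.**
- Regions within one metric: FA is tested at 0.05/3 = 0.0167.
- All 3 x 4 = 12 tests: the threshold is 0.05/12 = 0.0042. At d = 0.9 power is 43%, against 64% at 0.05/3. The family error is held at or below 5%; it is 3.4-3.9% under the assumed correlations.
- Separate families per region or per metric: with nothing correcting across families, the chance of any false positive among the DTI tests is about 9-11% or 12-14% under one set of assumed correlations, and 8.9-13.5% for the per-metric case under another.

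**The case against.** A reader might infer more: that the plan applies Bonferroni across four tensor metrics, that FA therefore loses about 20 points of power, or that the real error rate is 9-14%. The article does not support this. It says the four metrics will be computed and that correction is applied within ROI families; it nowhere says the correction runs over metrics. The two harms also exclude each other. The 20-point loss (64% to 43%) needs the 12-test family, in which error is controlled. The 9-14% needs families split by region or by metric. On the most literal reading, regions within a metric, FA is already tested at 0.05/3 and loses nothing relative to FA-only testing. The make-up of a family described as predefined may well stand in Supplementary material 3, so its absence from the article is not a fault.

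Nor does the redundancy of MD drive the result, since removing it is worth about 4 points. FA is the motivated marker within DTI only: section 2.6.2.4 describes the nigral iron and neuromelanin changes as pathognomonic, and nothing ranks FA above them. All of these objections stand.

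It can also be said that Bonferroni is valid and the trial exploratory, so that the choice is a matter of taste. Validity is granted. But Holm has the same validity and at least as much power under every reading of the family, so retaining Bonferroni buys no extra error control. One modest point in its favour is that Bonferroni has simple matching simultaneous confidence intervals, which Holm does not.

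**Conclusion.** The point holds as a minor improvement of method. Holm's superiority over the stated Bonferroni rule needs no assumption about effects, correlations or the content of the family. The size of the gain does: roughly 5 to 10 points of average power per test for three regions if all respond with d between 0.6 and 0.9 at 20 per arm, and close to nothing if one region responds. The power loss of about 20 points and the any-metric error of 9-14% are alternative scenarios that depend on unstated definitions and assumed inputs; neither should be reported as a property of this plan. Ranking FA first among the DTI metrics is a reasonable option, consistent with how the fMRI seeds are handled, but it is a trade-off and its absence is not an error.

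**What to change.** In section 2.9.2, name Holm in place of Bonferroni in the sentence on ROI-based comparisons and leave the predefined families as they are. This is a change of wording before analysis, with no extra data, visits or loss of error control. Where simultaneous intervals are wanted, Bonferroni intervals can be shown beside the Holm-adjusted p-values.

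Optionally, follow the primary-seed rule and name FA in the three regions as the primary DTI family, with MD, RD and AD secondary, noting that MD is determined by AD and RD. The cost is weaker inference on the diffusivities, which the sponsor should weigh against the exploratory aim.

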This study aims to: (1) conduct a triple-arm randomized controlled trial to evaluate the clinical efficacy of QNT in PD, and (2) integrate multimodal MRI to map functional connectivity reorganization, gray matter volume changes, white matter integrity, nigral iron deposition, and neuromelanin preservation, thereby identifying neuroplasticity targets induced by acupuncture.

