##### Susceptibility-Weighted Imaging (SWI) and Neuromelanin MRI (NM-MRI)

2.6.2.4

In PD, iron accumulation in nigrosome-1 and neuromelanin depletion in the substantia nigra pars compacta (SNc) are pathognomonic (36). SWI detects iron deposition via phase-sensitive contrast (37), whereas NM-MRI tracks neuromelanin loss through T1-shortening effects (38), offering high diagnostic specificity for early PD detection. Imaging protocols: SWI will be acquired using a 3D flow-compensated gradient-echo (GRE) sequence, saving both magnitude and phase images (TR/TE = 27/20 ms, flip angle = 15°, voxel size = 1 × 1 × 1 mm3, slice thickness = 1 mm, acquisition time ≈ 5–7 min). NM-MRI will be acquired using a T1-weighted turbo spin-echo sequence (TR/TE = 600/13 ms, slice thickness = 2.5 mm, field of view = 220 × 220 mm^2^, acquisition time ≈ 8 min).

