Building on emerging evidence supporting acupuncture's neuromodulatory effects, multimodal neuroimaging provides a robust framework to systematically decode its mechanisms. Evidence suggests it may modulate basal ganglia-thalamocortical circuits (44), increasing regional blood flow (45) and activating cortical metabolic pathways (46) supporting its neuromodulatory effects. Preclinical studies have demonstrated that acupuncture at ST36 (Zusanli) reduces basal ganglia, limbic, and cerebellar BOLD signals in PD models (47), whereas human trials have revealed enhanced neural responses in the substantia nigra, caudate, thalamus, and putamen following GB34 (Yanglingquan) stimulation (48). We hypothesize that QNT may promote the functional reorganization of the basal ganglia-thalamocortical circuits and associated motor networks through stimulation of acupoints, and may ameliorate pathological iron deposition in the substantia nigra, potentially via the modulation of these neural circuits. If the QNT demonstrates positive effects on neuroplasticity and symptom alleviation, this study will provide high-level mechanistic evidence supporting the integration of acupuncture into standardized neurorehabilitation protocols for PD.

This trial has several strengths: first is intervention optimization, minimal number of acupoints, no needle retention, rapid efficacy, and high safety increase patient compliance and reduce needle phobia. Second, multimodal MRI technology will be utilized to quantitatively assess gray matter volumetry (VBM), analyze default mode-sensorimotor network connectivity (rs-fMRI), evaluate white matter integrity (DTI), and quantify iron deposition (SWI) and neuromelanin signal intensity (NM-MRI) to map neuroplasticity targets. Third, the integration of clinical scales, biomechanical indices and neuroimaging biomarkers provides robust mechanistic validation. Fourth, triple-arm randomization (verum acupuncture, sham acupuncture, waitlist control) with strict allocation concealment, SPAD blinding protocols, and post-trial blinding assessment ensures internal validity.

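### The plan promises nigral iron and neuromelanin signal, but the SWI and NM-MRI measures named in its analysis text are only an area and widths

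*Protocol article*

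**What the plan says.** On what the trial sets out to learn:

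- Section 2.6.1 (Clinical outcomes): "the primary endpoint is the change in multimodal MRI biomarkers". No single marker is singled out.
- The Abstract (Methods) lists five kinds of MRI marker, two of which are nigral iron deposition and neuromelanin content. Aim 2 in the Introduction names "nigral iron deposition, and neuromelanin preservation".
- The Discussion hypothesises that the needle therapy "may ameliorate pathological iron deposition in the substantia nigra". Among the strengths it says the trial will "quantify iron deposition (SWI) and neuromelanin signal intensity (NM-MRI".
- The closing paragraph of the Discussion plans to correlate nigral iron with clinical outcomes in support of causal claims.

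On how the two sequences work and what is stored (section 2.6.2.4): "SWI detects iron deposition via phase-sensitive contrast", while NM-MRI is said to follow neuromelanin loss through T1 shortening. The SWI acquisition is described as "saving both magnitude and phase images".

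On what is extracted (section 2.9.2): phase images are high-pass filtered "before manual delineation of substantia nigra (SN) area and measurement of SN pars compacta (SNc) width". For the other sequence, "NM-MRI SNc width will be measured in the dorsoventral direction", on one chosen axial slice. Agreement between raters is assessed for all manual measurements, and the two raters' values are averaged.

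**The concern.** Iron content and neuromelanin signal are properties of the tissue signal inside a region. Area and width describe the size of the region that a rater can see. The plan promises the first kind of quantity and names only the second.

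What is at stake is the interpretation of the result. If SNc width does not change, the natural report under this plan is that the therapy had no effect on iron or neuromelanin. If it does change, the natural report is that iron or neuromelanin changed. Neither statement would rest on a measured value of the quantity it names, and the nigral iron result is also meant to feed the correlation with clinical outcomes.

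**Working it through.** No figure in the plan depends on this point, so there is no stated number to reproduce. The check sets promise, physical basis and measure side by side for each sequence.

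**NM-MRI**
1. Promise: neuromelanin content (Abstract), its preservation (aim 2), its signal intensity (Discussion).
2. Basis given in section 2.6.2.4: T1 shortening, a signal property.
3. Measure named in section 2.9.2: SNc width, in a stated direction, on one slice, on a named workstation. No intensity, contrast or reference region is named.
4. Result: signal intensity and width are different variables, so the Discussion and section 2.9.2 cannot both describe the NM-MRI outcome. This is a direct contradiction.

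**SWI**
1. Promise: nigral iron deposition (Abstract, aim 2, hypothesis), to be quantified (Discussion).
2. Basis given in section 2.6.2.4: phase contrast, again a signal property.
3. Measures named in section 2.9.2: SN area by manual outline and SNc width. No phase or susceptibility value is named.
4. Result: nothing named is an iron-related value. The outline may have been meant as a region from which to take one, but the text does not say so.

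**Comparison within the same section.** For DTI, section 2.9.2 names both the regions (substantia nigra, putamen, caudate) and the values computed (FA, MD, RD, AD). For SWI and NM-MRI it names only dimensions. The section therefore does name the extracted quantity where it intends one.

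**What a dimension can and cannot show.** Suppose the mean signal inside the SN changes while the visible border stays put: area and width record no change. Suppose instead that the border is drawn differently at week 4: area and width record a change with no change in signal. The visible border does depend on contrast, so a dimension may follow signal to some degree. The article gives no relation between the two and no reason to expect one over a 4-week interval. Section 2.6.2.4 supports these sequences for early detection of PD, a diagnostic use.

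**Extent.** Two of the five kinds of marker in the Abstract are affected: 2/5 of the list. The other three (gray matter volume, functional connectivity, white matter integrity) are not touched by this point.

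**The case against.** Four arguments deserve weight.

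*Supplementary material 3 may hold the missing measure.* Section 2.9.2 refers to it for full detail and it is not shown. A reader might infer that iron and neuromelanin signal are never quantified in this trial; the documents do not support that, and the point is limited to the text shown. The contradiction remains, because section 2.9.2 does not leave the measure open. If the supplement has a signal-based measure, the article still needs to be brought into line with it.

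*The SWI outline may be a region and not an outcome.* This is a fair reading, since the same verb is used for the DTI regions. It makes the SWI half an unclear definition and not a proven absence. It does not help NM-MRI, where width is plainly the measure.

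*Area and width may be usable proxies.* They may be, but the article neither says so nor argues it. Averaging two raters and checking their agreement improves repeatability; it does not turn a width into a content.

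*The trial is exploratory.* Section 2.3 says so. But the imaging set is still called the primary endpoint, and an exploratory result must also be named for what was measured.

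Two further readings go too far. The hypothesis sentence names iron only, so neuromelanin rests on the Abstract, aim 2 and the strengths paragraph. And the plan sets one undifferentiated MRI endpoint, not five separate primary endpoints, so it would be wrong to say that two primary endpoints fail.

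**Conclusion.** The point stands in this form: the visible text promises iron and neuromelanin signal and names only dimensions. The contradiction is direct for NM-MRI. For SWI, no iron-related value is named and the role of the SN outline is unclear. It concerns two of the five listed kinds of marker and the one imaging change that the hypothesis ties to the substantia nigra. It should be settled before analysis, because it decides what the trial can conclude about iron and neuromelanin.

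The conclusion rests on the article alone and assumes nothing about Supplementary material 3.

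No numerical size is claimed. A reader might set the 1 mm SWI voxel against an assumed SNc width of 3 to 5 mm and obtain 1/5 = 20% to 1/3 = 33% for one voxel of edge placement. The documents give no SNc width and no placement error, two raters are averaged, and no in-plane NM-MRI voxel size is stated. That figure is at most an SWI-only illustration, and the verdict does not depend on it.

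**What to change.** Preferred route: name one signal-based outcome per sequence, with its region, reference and unit, before analysis.

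- NM-MRI: the ratio of SNc signal to the signal of a stated reference region.
- SWI: the mean phase value within the SN, stating whether it is taken before or after high-pass filtering. Susceptibility should be named only if the saved phase data allow it; the article says that phase images are saved, not that they are unfiltered or suited to that reconstruction.
- Use the same region definition at baseline and week 4, and keep SN area and SNc width as secondary morphometry.

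This uses images the plan already collects, so no scan or visit is added. The cost is some extra offline processing, and width loses its leading role.

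Alternative route: call the endpoints SN area and SNc width, and limit the iron and neuromelanin claims to what these dimensions can show. This is a change of text only, but the trial then gives up a direct answer on iron and neuromelanin.

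On either route, align the Abstract, aim 2, section 2.9.2 and the Discussion (hypothesis, strengths and closing paragraph), and check them against Supplementary material 3.

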#### Multimodal MRI data

2.6.2

Multimodal MRI data will be acquired at baseline and post-treatment (week 4) via a Siemens Prisma 3.0T scanner (64-channel head coil). All scans will be performed between 4:00–6:00 p.m. Participants will be scanned in the practical “ON” medication state, approximately 1 h after their regular afternoon dopaminergic medication to maintain a uniform medication condition and minimize motion artifacts caused by motor symptoms. No specific dietary restrictions are required before scanning. The post-treatment scan will be scheduled within 24 h after the final acupuncture session. Structural and functional imaging protocols include the following structural markers: T1-weighted imaging (T1WI), T2-weighted imaging (T2WI), T2-Flair imaging, diffusion tensor imaging (DTI), neuromelanin-sensitive MRI (NM-MRI), and susceptibility-weighted imaging (SWI). Functional markers: blood oxygen level-dependent functional MRI (BOLD-fMRI). Detailed acquisition parameters, quality control procedures, preprocessing, and statistical thresholds are provided in Supplementary material 3.

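### The neuromelanin endpoint is a change between two scans, but its slice rule suits a single scan, and the planned inter-rater ICC need not reveal the noise this adds

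*Protocol article*

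**What the plan says.** Section 2.6.1 makes MRI primary: "the primary endpoint is the change in multimodal MRI biomarkers". Section 2.6.2 places the two scans at baseline and week 4. Neuromelanin is one of the markers named in the abstract and in the study aims.

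For NM-MRI, section 2.6.2.4 gives a T1-weighted turbo spin-echo sequence with "slice thickness = 2.5 mm". The only neuromelanin measure in section 2.9.2 is a manual width of the substantia nigra pars compacta (SNc): "NM-MRI SNc width will be measured in the dorsoventral direction on the optimal axial slice using the ADW4.6 workstation".

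On reliability, the same section says "ICC will be assessed for all manual measurements, and the average of the two raters will be used for analysis". The only kind of ICC it describes is inter-rater, and the threshold of 0.80 is written for the DTI regions. Reader blinding also appears in the DTI sentence, where regions are "manually delineated on FA color maps by two independent raters blinded to group and time point".

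Sections 2.6.2 and 2.9.2 refer further imaging detail to Supplementary material 3, which is not shown.

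**The concern.** A rule that picks the best slice in a scan is reasonable for a single cross-sectional reading. The endpoint here is a difference between two readings of the same patient taken 4 weeks apart. Section 2.9.2 states the direction of measurement, the workstation, the slice rule and the reliability check, but nothing that ties the week-4 plane to the baseline plane: no landmark, no alignment of the two scans, no slice matching. If the plane sits at a different level, or the head is tilted differently, another cross-section of the nigra is measured, and the discrepancy passes straight into the change.

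The stated safeguard does not test this weak point. Two raters who read the same scan share its head position. If they also share the slice, they share the slice error. An inter-rater ICC counts such shared error as difference between patients, so it can look good while the change is unreliable.

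What is at stake is precision for one primary marker. Section 2.3 took the group size from general fMRI recommendations, not from the variability of a change in SNc width, so nothing in the sample size allows for this extra noise.

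**Working it through.** **The plan's own figure.** Section 2.3 starts from 20 per group and allows 10% attrition: 20/0.9 = 22.2, so 23 per group and 69 in all. This reproduces exactly. The point disputes no stated number.

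**Variance model (components are assumptions; the document gives none for NM-MRI).** Set the variance of a single reading at one visit to 1 = T + S + E, where
- T is the true variance between patients,
- S is the variance from slice level and head position, drawn anew at each visit,
- E is the reading error of one rater.

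If both raters read the same slice:
- inter-rater ICC = (T + S)/(T + S + E)
- scan-rescan reliability of the two-rater mean = T/(T + S + E/2)
- variance of the change in the two-rater mean = 2(S + E/2), with the true change taken as constant
- difference between two arms detectable with 80% power, two-sided 0.05, uncorrected, n = 20 per group = (1.96 + 0.84) × SD of change × √(2/20)

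Hold the inter-rater ICC at 0.90, so E = 0.10 and T = 0.90 − S:

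| S | Inter-rater ICC | Rescan reliability | Variance of change | SD of change | Detectable difference |
|---|---|---|---|---|---|
| 0 | 0.90 | 0.90/0.95 = 0.95 | 2(0 + 0.05) = 0.10 | 0.32 | 0.28 |
| 0.1 | 0.90 | 0.80/0.95 = 0.84 | 2(0.1 + 0.05) = 0.30 | 0.55 | 0.49 |
| 0.2 | 0.90 | 0.70/0.95 = 0.74 | 2(0.2 + 0.05) = 0.50 | 0.71 | 0.63 |
| 0.3 | 0.90 | 0.60/0.95 = 0.63 | 2(0.3 + 0.05) = 0.70 | 0.84 | 0.74 |

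The last two columns are in units of the single-reading SD. With the ICC at 0.80, the threshold written for DTI, S from 0 to 0.3 takes rescan reliability from 0.80/0.90 = 0.89 to 0.50/0.90 = 0.56, again with the ICC unchanged.

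**If each rater chooses a slice alone.** Let independent slice choice have variance 0.2, with E = 0.10 and T = 0.70. The ICC now falls to 0.70, so it does register the problem. Averaging also helps: the variance of change is 2 × (0.2 + 0.1)/2 = 0.30 (SD 0.55), against 0.50 (SD 0.71) with a shared slice. If the same 0.2 comes from head position, the ICC stays at 0.90 and rescan reliability is 0.74 whether or not the raters choose separately. A simulation of 200,000 patients gave the same values.

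**Geometry.** Assume contiguous 2.5 mm slices, random positioning and readers who aim at the same level. The nearest slice centre lies at most 2.5/2 = 1.25 mm from that level at each visit. The offset has SD 2.5/√12 = 0.72 mm, and the difference between visits has SD 0.72 × √2 = about 1.0 mm. How much the width changes over that distance is not given.

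**The case against.** The strongest reply is that this is reading-manual detail. The article sends imaging detail to Supplementary material 3, and it nowhere says in words that the slice is chosen separately at each visit. A matching rule may already exist. That stands as a condition on the fix. It does not remove the point, because the article does state a slice rule, and the rule it states is one for a single scan.

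Three stronger readings are tempting and are not supported.

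- A reader might infer that the plane must move by at least one slice thickness between visits. It need not. When readers aim at the same level, 1.25 mm per visit is the limit, and repositioning and tilt can be much smaller. A full 2.5 mm step arises only if a different level is chosen, which the text does not say.
- A reader might infer that neither the ICC nor averaging touches slice choice. That holds only if both raters use one shared slice. If each chooses alone, the ICC falls and averaging halves the choice variance. Only head position escapes both in every case.
- A reader might infer that the readings are unblinded and could manufacture an effect. Section 2.9.2 does not repeat the blinding phrase for NM-MRI, but its later mention of the two raters most naturally means the pair already described as blinded. Silence is not a statement that readers are unblinded.

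It is also fair that the trial calls itself exploratory, uses one scanner with two technicians, and treats neuromelanin as one of several markers. This limits the consequence but not the mechanism.

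**Conclusion.** The point holds as a loss of precision in one primary marker. The stated slice rule does not secure the same anatomical level at both visits, so level and head-position differences enter the change score, and the inter-rater ICC can stay high while they do.

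The size cannot be derived from the document, which gives no SNc width, no variation of width along the nigra and no repeat-scan error. The illustrative range shows only that the loss could be material. At an ICC of 0.90, an assumed share of 0.1 already triples the variance of the change (0.10 to 0.30), and hence the number of patients needed for a given difference. It rests on assumed components, a constant true change and no multiplicity correction.

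With blinded readers the error has the same distribution in all randomised arms. It does not by itself bias the arm comparison, and no claim of bias is made here.

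**What to change.** Unless Supplementary material 3 already does this, replace the slice rule in section 2.9.2 with one that serves a change:

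- Define the measurement level by a fixed anatomical landmark and measure both visits at that level. One route is to align each patient's two NM-MRI scans rigidly to a within-patient midpoint space, so that both are resampled equally. Resampling only week 4 should be avoided, because its blurring would then enter the change. The other route is to pick landmark-matched native slices, with no resampling.
- Have the two raters read both visits in random order.
- State that blinding to group and time point covers the SWI and NM-MRI readings as well as the DTI regions.

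If the supplement already holds such a rule, one sentence in section 2.9.2 pointing to it is enough.

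The scans and raters stay the same. The cost is one alignment or matching step per patient and, if the scans are resampled, slight blurring that is equal at both visits.
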